## Abstract

**Background:**

Knowledge translation (KT) research in long-term care (LTC) is still in its early stages. This protocol describes the evaluation of a multifaceted, interdisciplinary KT intervention aimed at integrating evidence-based osteoporosis and fracture prevention strategies into LTC care processes.

**Methods and design:**

The Vitamin D and Osteoporosis Study (ViD*OS*) is underway in 40 LTC homes (n = 19 intervention, n = 21 control) across Ontario, Canada. The primary objectives of this study are to assess the feasibility of delivering the KT intervention, and clinically, to increase the percent of LTC residents prescribed ≥800 IU of vitamin D daily. Eligibility criteria are LTC homes that are serviced by our partner pharmacy provider and have more than one prescribing physician. The target audience within each LTC home is the Professional Advisory Committee (PAC), an interdisciplinary team who meets quarterly. The key elements of the intervention are three interactive educational sessions led by an expert opinion leader, action planning using a quality improvement cycle, audit and feedback reports, nominated internal champions, and reminders/point-of-care tools. Control homes do not receive any intervention, however both intervention and control homes received educational materials as part of the Ontario Osteoporosis Strategy. Primary outcomes are feasibility measures (recruitment, retention, attendance at educational sessions, action plan items identified and initiated, internal champions identified, performance reports provided and reviewed), and vitamin D (≥800 IU/daily) prescribing at 6 and 12 months. Secondary outcomes include the proportion of residents prescribed calcium supplements and osteoporosis medications, and falls and fractures. Qualitative methods will examine the experience of the LTC team with the KT intervention. Homes are centrally randomized to intervention and control groups in blocks of variable size using a computer generated allocation sequence. Randomization is stratified by home size and profit/nonprofit status. Prescribing data retrieval and analysis are performed by blinded personnel.

**Discussion:**

Our study will contribute to an improved understanding of the feasibility and acceptability of a multifaceted intervention aimed at translating knowledge to LTC practitioners. Lessons learned from this study will be valuable in guiding future research and understanding the complexities of translating knowledge in LTC.

**Trial registration:**

ClinicalTrials.gov NCT01398527.

## Background

The field of knowledge translation (KT) attempts to bridge the gap between the generation of research evidence and the application of this evidence into clinical practice. KT is commonly defined as ‘a dynamic and iterative process that includes synthesis, dissemination, exchange and ethically-sound application of knowledge’ [1]. Examining the effectiveness of KT strategies across different contexts, healthcare professions, and target behaviors is essential [2] if we are to effectively bridge the gap between research evidence and clinical practice. To guide decision makers in choosing the best implementation strategies, rigorous evaluations of KT programs, including well-designed cluster randomized trials, are needed [3].

Despite a growing body of KT evidence in acute care or community settings, KT research in long-term care (LTC) is still in its early stages [4-6]. Recent LTC initiatives have examined the role of organizational context and/or developed empirically-based theories related to KT in LTC [7-9]. However, few studies within the LTC setting have focused on evaluating the effectiveness of common behaviour change strategies (*e.g.*, audit and feedback, educational materials, reminders) [10,11], particularly those involving multifaceted interventions. In a recent scoping review by Bostrom *et al.*[5], only 3.6% (n = 61) of KT studies identified were related to older adults, and approximately one-half of them were done in LTC. Problematic is the fact that the majority of these studies were not targeted at the organizational level, did not report on system level outcomes, and included only a single KT strategy (*e.g.*, audit and feedback alone). The majority of KT interventions, regardless of setting, have not targeted the entire interdisciplinary team (*i.e.*, physicians, nurses, pharmacists, dietitians, rehabilitation therapists, and other professionals) [12]. Of the LTC studies in the Bostrom review [5], 60% did not target mixed professional groups despite the emphasis on collaboration among the disciplines practicing in LTC [13]. Previous multifaceted interventions for interdisciplinary teams have had some success within the LTC setting [14,15].

Implementing evidence into practice requires whole system change [2,16], particularly in the LTC setting [5,17]. Berta *et al.*[6] suggest the majority of factors that may enhance the uptake and use of evidence-based practices in LTC are organizational and include: a working culture that facilitates cooperation and knowledge exchange; standardization of activities; experienced clinical leaders that engage others in the process; and ultimately the incorporation of guidelines that are reinforced by regulatory bodies. Other factors that enhance implementation of evidence-based practices in LTC include strong leadership [17-19], medical directives, and building best practices recommendations into training materials [20].

### Identifying the knowledge-to-action gaps

The topic of our KT intervention is evidence-based osteoporosis management and fracture prevention strategies [21-27]. Previous research by our team indicates that many LTC providers are unaware of osteoporosis and fracture prevention best practices, or have concerns surrounding diagnosis and treatment in elderly patients [28,29]. Furthermore, as a recent survey of LTC Medical Directors and Directors of Nursing documented, barriers to fracture care were modifiable and could be overcome through education and changes to local care delivery systems [30]. Rather than focusing on individual providers, we propose a model that takes a more collective approach and emphasizes integrating evidence-based practices into care processes.

In addition to proper assessment of individuals at high risk for fracture [21], we are emphasizing the wide-scale implementation of adequate levels of vitamin D (≥800 IU/day) because it is a tolerable, low-cost intervention with strong evidence that it can prevent fractures and falls in LTC residents [22,24,26,27,31]. In an environmental scan of 15 LTC homes we conducted in 2008 (n = 3,132 residents), the overall rate of vitamin D use was 38% [32], and there was considerable variation between homes with rates ranging from 11 to 62%. Another study [33] we conducted using data collected via the Resident Assessment Instrument (RAI) 2.0 [34,35] found similar results.

We developed a multifaceted, interdisciplinary KT intervention to improve the use of evidence-based osteoporosis and fracture prevention practices in LTC homes. The current report outlines the research design and protocol for evaluating this KT intervention.

## Methods

### Study population

The Vitamin D and Osteoporosis (ViD*OS*) study is currently underway in 40 LTC homes (19 intervention and 21 control) in Ontario, Canada. In Canada, LTC homes (also known as nursing homes or homes for the aged) are government-regulated facilities designed for individuals who require onsite nursing care, 24-h supervision, or personal support [36]. Our recruitment strategy included LTC homes located in communities of all sizes and geographical regions across the province of Ontario.

In order to make this study as generalizable as possible, we have only two facility-level eligibility criteria, and no patient-level criteria. All LTC homes serviced by our partner pharmacy provider (Medical Pharmacies Group Limited) and who have more than one prescribing physician (at the time of recruitment) were eligible for recruitment into the study. Medical Pharmacies is a large pharmacy provider whose services include medication packaging and distribution, clinical support, and consulting services to approximately one-third of all LTC homes in Ontario. Our rationale for excluding LTC homes with only one treating physician is to maintain anonymity during the presentation of prescribing reports at educational sessions. Furthermore, the requirement of having at least two physicians per home decreases sample size as it contributes to a lower intracluster correlation coefficient [37].

### Aims and objectives

The aim of the ViD*OS* study is to evaluate the feasibility and effectiveness of a multifaceted KT intervention to better integrate evidence-based osteoporosis and fracture prevention care processes in LTC. In addition to measuring feasibility of the intervention, the primary clinical objective is to determine if the intervention can increase the proportion of residents who are prescribed adequate levels of vitamin D (≥800 IU/day). Secondary objectives include: to determine if the intervention increases the prescribing of calcium supplements (≥500 mg/day elemental calcium); to determine if the intervention increases the prescribing of osteoporosis medications in high-risk individuals (*i.e.*, documented osteoporosis or prior hip fracture); to understand the experience of the LTC team with the intervention and which components were perceived as feasible, acceptable, and effective; and to document falls and fractures occurring during the study period.

### Study outcomes

#### Feasibility

Feasibility outcomes are measured at the facility-level and include (some are only relevant to intervention homes): the proportion of homes that are recruited and retained, attendance of Medical Directors and other professionals at educational sessions, internal champions identified, action plan items identified and initiated, performance reports provided and reviewed, falls and fracture data collection completed. A criterion of ≥80% will be used as the criterion for success on each of these feasibility measures, with the exception of recruitment. Other cluster randomized controlled trials (RCTs) in nursing homes aimed at changing the behaviour of health professionals have noted recruitment in the 40 to 50% range [38-40], thus our recruitment criterion for success was 40%.

#### Clinical

The primary clinical outcomes are the proportion of residents prescribed vitamin D ≥800 IU/day at 6 and 12 months. The secondary prescribing outcomes are the proportion of residents prescribed ≥500 mg/day of elemental calcium and the proportion of high risk residents (*i.e.*, those with a fracture or documented osteoporosis) prescribed an osteoporosis medication (oral and IV bisphosphonates, teriparatide, denosumab) at 6 and 12 months. Other secondary outcomes include the number of falls, hip fracture and all fracture (hip, wrist, spine, foot, humerus, ribs, clavicle, ankle, other) for the data collection periods (*i.e.*, three months of falls and fracture data collected three times during the study, see Figure 1).

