### Data analysis

#### Quantitative analysis

Data from the trial will be analyzed and reported in accordance with the CONSORT criteria [41,63,64]. The baseline characteristics will be reported as mean (standard deviation) or median (minimum, maximum) values for continuous variables and as counts (percent) for categorical variables. The primary feasibility outcomes will be analyzed using descriptive statistics expressed as percent and corresponding 95% confidence intervals (CI). Our primary analyses will be performed using the intention-to-treat principle. The generalized estimating equations (GEE) technique, assuming an exchangeable correlation structure [65], will be used to determine differences between groups for the proportion of residents prescribed vitamin D, calcium and other osteoporosis medication, and number of fractures or falls. The GEE method will take into account the clustered nature of the data, given that residents treated within a LTC home are expected to be similar or correlated (clustered variable will be the LTC home). For the model, the unit of analysis will be the resident and the unit of inference will be the home. There is an increased risk of imbalance at the resident-level because of the home-level randomization. Therefore, resident baseline characteristics that will be included in this analysis are: age, gender, co-morbidities, and the number of prescribed medications. Unadjusted and adjusted odds ratios (OR) and corresponding 95% CIs will be reported. All statistical analyses will be performed using the SAS/STAT 9.2 software package (SAS Institute Inc., Cary, NC, USA) with the criterion for statistical significance set at α ≤0.05.

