#### Sample size

Our sample size was calculated to detect a difference in the percentage of residents prescribed ≥800 IU/daily vitamin D at follow-up in the intervention versus control groups. We assumed an average of 120 residents per LTC home and that 30% of residents were prescribed ≥800 IU/daily vitamin D at baseline [33]. We postulate a 20% increase in vitamin D prescribing in the intervention group and a 5% increase in the control group (to account for the potential impact of other province-wide initiatives such as the *Ontario Osteoporosis Strategy for LTC*). Based on these assumptions, to detect a 15% difference in prescribing between the groups with an intracluster correlation of 0.10 (two-sided test with significance = 0.05), a sample size of 2,160 residents from 18 LTC homes in each of the intervention and control groups is required to achieve 82% power. Factoring in a potential 10% dropout rate, the recruitment target was 40 LTC homes (20 = intervention, 20 = control).

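### Two primary time points for vitamin D prescribing share one undivided 5% level, the sample size covers one unnamed time point, and no rule says which result decides

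*Protocol article*

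**What the plan says.** The outcome section (Study outcomes, Clinical) uses the plural: "The primary clinical outcomes are the proportion of residents prescribed vitamin D ≥800 IU/day at 6 and 12 months". The abstract repeats it, listing "vitamin D (≥800 IU/daily) prescribing at 6 and 12 months" beside the feasibility measures. Neither place ranks the two time points.

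Under Quantitative analysis, one GEE description serves all prescribing, fall and fracture outcomes, "with the criterion for statistical significance set at α ≤0.05". The same paragraph expects resident-level imbalance, lists the baseline covariates that the analysis will include, and adds: "Unadjusted and adjusted odds ratios (OR) and corresponding 95% CIs will be reported".

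The Sample size section begins: "Our sample size was calculated to detect a difference in the percentage of residents prescribed ≥800 IU/daily vitamin D at follow-up". It does not say which follow-up is meant. The calculation is for a single "two-sided test with significance = 0.05".

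Three further statements bear on the point. Study design describes a pilot that puts feasibility first and an intervention lasting 12 months. The intervention section places the educational sessions about six months apart. Data monitoring rules out any formal comparison of the arms before the end of the study.

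**The concern.** The article fixes three things that do not fit together: two primary clinical outcomes, one undivided 5% level, and a power calculation for one comparison. If success at 6 months or at 12 months can carry the claim that the intervention raised prescribing, the 5% level applies to each test but not to the claim.

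The interpretation suffers as well. At 6 months the homes have had about half of a 12-month intervention, so the two results could well differ. An early gain that fades, or a gain that appears only after full delivery, would leave one significant and one non-significant primary outcome. The article does not say what would then be concluded, so the reading would be chosen after the results were known.

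**Working it through.** **Inputs from the Sample size section:** 120 residents per home; 18 homes (2,160 residents) per arm; intracluster correlation 0.10; 30% baseline; increases of 20 and 5 points, so 50% against 35%; two-sided 0.05; stated power 82%.

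**1. The plan's own figure.**
- Design effect = 1 + (120 − 1) × 0.10 = 12.9.
- Effective sample per arm = 2,160 / 12.9 = 167.4.
- Unpooled normal power for 35% v 50%: SE = √[(0.35×0.65 + 0.50×0.50)/167.4] = 0.0534. Then 0.15/0.0534 = 2.81, and Φ(2.81 − 1.96) = 80.2%. The pooled version gives 79.6%.
- For 30% v 45% the figures are 81.9% unpooled and 81.2% pooled.
- Homes: 36 / 0.9 = 40, as stated.

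The stated 82% is therefore reproduced to within about two points, for **one** comparison at 0.05.

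**2. Type I error with two time points.** Let Z₁ and Z₂ be the 6- and 12-month test statistics, bivariate normal with correlation ρ and no true effect at either time. The article gives no ρ, so a range is assumed.
- Either significant: 1 − P(|Z₁|<1.96, |Z₂|<1.96)
- Either significant in favour of the intervention: 1 − P(Z₁<1.96, Z₂<1.96)
- Both significant: 0.05 + 0.05 − P(either significant)

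| ρ (assumed) | Either, two-sided | Either, benefit only | Both |
|---|---|---|---|
| 0.50 | 9.07% | 4.54% | 0.93% |
| 0.70 | 8.35% | 4.17% | 1.65% |
| 0.80 | 7.81% | 3.90% | 2.19% |
| 0.90 | 7.04% | 3.52% | 2.96% |
| 0.95 | 6.46% | 3.23% | 3.54% |

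The reference values are 5% two-sided and 2.5% for benefit only. Under an either-suffices rule the error exceeds its reference at every ρ below 1. Under a both-required rule it does not.

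**3. Cost of the alternatives** (pooled formula).

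| Rates | Power, 18 homes per arm, 0.05 | Power, 18 homes per arm, 0.025 | Homes per arm for 82%, 0.05 | Homes per arm for 82%, 0.025 |
|---|---|---|---|---|
| 35% v 50% | 79.6% | 70.6% | 19.2 | 23.2 |
| 30% v 45% | 81.2% | 72.6% | 18.4 | 22.3 |

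Splitting alpha equally costs about 9 points of power at each time point (79.6 − 70.6 = 9.0; 81.2 − 72.6 = 8.6), or about 4 homes per arm (23.2 − 19.2 = 4.0; 22.3 − 18.4 = 3.9). A single primary time point costs neither.

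**The case against.** The strongest reply is that the article never says success at either time point is enough. It gives one general analysis description and one general criterion. If the intention was to require both, the error is below 5% and nothing is inflated. A decision rule is also the kind of detail that a condensed article leaves to the full protocol or SAP. This stands in part: a reader might infer that the plan allows a claim from either time point and so has an error rate above 5%, but the text supports only the conditional statement. It does not dispose of the point. The article itself names two primary outcomes, sets the level and sizes the trial for one comparison. Those published statements would still have to be brought into line with any rule written elsewhere.

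Secondly, a reader might count the unadjusted and adjusted odds ratios as further chances of success. Four tests with free choice among them would give about 9% to 14% under assumed correlations (0.8 to 0.95 between models, 0.5 to 0.9 between time points). The document does not support that reading. Quantitative analysis names the covariates in advance and gives the reason for including them, which points to the adjusted model, and reporting both odds ratios is ordinary transparency. All that is missing is a statement that the adjusted result decides.

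Thirdly, the two-sided figures also count false findings of harm, and the same homes are measured twice, which argues for the higher correlations and the smaller excess. Both remarks are fair, and for that reason the benefit-only column and the range are shown.

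Finally, the trial is a feasibility-first pilot with no formal comparison before its end. That lowers the severity. It does not remove the issue, since the stated aim includes effectiveness and this outcome is both powered and formally tested.

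**Conclusion.** The point holds in conditional form. Two primary time points share one undivided 5% level, and the sample size is tied to neither by name. If either may carry the claim, the two-sided type I error is about 6.5% to 9.1%, and the chance of a false claim of benefit is 3.2% to 4.5% against 2.5%. These figures rest on an assumed correlation between 0.95 and 0.5 and on the either-suffices reading, which the article neither states nor excludes. Independently of those assumptions, a result that is positive at one time point only has no defined conclusion.

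Severity is moderate: the trial is a pilot that puts feasibility first, and the feasibility outcomes are descriptive and unaffected.

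**What to change.** Name vitamin D prescribing at 12 months, the end of the intervention period, as the single primary clinical outcome, and name 12 months in the Sample size section. Make 6 months secondary, or test it at 0.05 only if the 12-month result is significant. State in the same place that the covariate-adjusted GEE already described decides, with the unadjusted odds ratio as supportive. Change the abstract to match.

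This takes about two sentences and no extra homes, and the stated power of about 80% to 82% stands. The small downside is that a benefit seen only at 6 months could no longer carry the primary claim. Requiring significance at both time points would also control the error without an alpha split, but each test would then have to succeed, so power would be lower than for one time point.

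The change should be dated before the arms are compared. Data monitoring defers that comparison to the end and the final analyst is blinded, so it can still be made cleanly. The date matters because intervention homes' prescribing is reported at each session by an analyst who is not blinded.

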**Table 1 T1:** **Key Components of the Multifaceted ViD *****OS *****intervention**

Interactive Educational Sessions	Presentation of three learning modules that include a summary of best practices, special considerations for assessing/treating the elderly, key messages, integration of OP/fracture prevention into care processes, and a case study. Opportunity for discussion and active participation via problem-based learning and completion of action plans.
Expert Opinion Leader/ Study Coordinator	Expert opinion leader leads first and second interactive educational sessions via webinar (with study coordinator facilitating on-site). A Geriatric Nursing Consultant leads the third interactive educational session via webinar.
DVD	A 10-min DVD, ‘Meeting the Challenge of Osteoporosis and Fracture Prevention,’ is viewed at the first interactive educational session (and a copy left for the team to educate other/new staff members, residents, families). This DVD was created by the * Osteoporosis Strategy for LTC* (http://www.osteoporosislongtermcare.ca[54]) and is specific to the LTC context.
Performance Reports (Audit and Feedback)	Performance reports for vitamin D, calcium, and osteoporosis medications prescribing (aggregated for all residents in a home) and benchmarked against other ViD*OS* intervention homes, are presented at each interactive educational session. Confidential, individual performance reports are also provided to each physician.
Reminders/Point of Care Tools	Treatment Alert: A tool used by consultant pharmacists to alert physicians and nurse practitioners to assess and consider osteoporosis treatment for residents at increased risk for fracture (based on the 2010 Osteoporosis Canada Clinical Practice Guidelines [21].
	X-ray Requisition Stamp: A stamp labeled ‘please rule out vertebral fractures’ to add to chest X-ray requisitions.
	Process Indicator Checklist: This tool assists teams with creating internal processes and policies that support and sustain appropriate prescribing and other osteoporosis and fractures best practices (*e.g.*, admission/quarterly assessment, diagnoses documentation, ongoing staff education and training).
Action Planning for Quality Improvement	Discussion/completion of a work-sheet to set specific action items for team members, address barriers and facilitators, and outline best practices strategies. Homes work on action plans between study sessions.

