#### Patient-level

Figure 2 provides an overview of the data collection time-line. De-identified clinical data including demographic, prescribing, and co-morbidities (from the Medication Administration Record) are collected from the pharmacy database by the Director of Systems Services at Medical Pharmacies ([name]).

Falls and fractures data for every resident are collected by a LTC staff member at each home for three-month periods at three times during the study (coinciding with prescribing data pulls, Figure 2). The information source used to populate the data collection spreadsheets may vary by LTC home and sources are documented by the study coordinator. With the recent wide-scale implementation of the RAI-2.0 assessments across Ontario LTC homes [34,35], future studies collecting information on falls and fracture data will likely use this as a data source. The RAI-2.0 is a standard assessment using common methodology and measures and is completed by trained assessors (typically within 14 days of admission and then on a quarterly basis).

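### The high-risk denominator of the osteoporosis-medication outcome has two conflicting definitions, and if it is read after the intervention starts it can depend on allocation

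*Protocol article*

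**What the plan says.** The Protocol article defines high risk twice, each time as an explanation of the term rather than as an example. In Aims and objectives it is "documented osteoporosis or prior hip fracture". In Study outcomes, Clinical, it is "those with a fracture or documented osteoporosis". The outcome is the proportion of that group "prescribed an osteoporosis medication (oral and IV bisphosphonates, teriparatide, denosumab) at 6 and 12 months".

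Table 1 lists the point-of-care tools of the intervention. They are an X-ray requisition stamp reading "please rule out vertebral fractures", a process checklist whose scope includes "admission/quarterly assessment, diagnoses documentation, ongoing staff education and training", and a treatment alert with which pharmacists "alert physicians and nurse practitioners to assess and consider osteoporosis treatment for residents at increased risk for fracture". The section on control homes says that they receive no intervention. The toolkit and website that reached all Ontario homes are described separately, and the stamp, checklist and alert are not listed among their contents.

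The Patient-level data section says that "co-morbidities (from the Medication Administration Record) are collected from the pharmacy database". No section states when a resident's high-risk status is fixed, or whether a fracture during the study qualifies.

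**The concern.** The objective and the outcome meant to answer it name different populations, so two analysts working from the same article could compute two different proportions.

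The second problem is one of design. A proportion is comparable between randomised arms only if allocation cannot influence who is counted below the line. Here, fracture and documented diagnosis are both the entry criteria for the denominator and things that the intervention encourages staff to look for and write down. If status is read at follow-up, the two arms may be compared on groups assembled by different recording practice. A difference could then arise without any change in prescribing, or a real change could be diluted or exaggerated.

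**Working it through.** The article gives no expected rate, effect or power for this outcome, so there is no planned figure to reproduce. The sample-size section concerns vitamin D only.

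**Step 1: are the two definitions equivalent?** No. The Clinical section lists hip fracture separately from "all fracture (hip, wrist, spine, foot, humerus, ribs, clavicle, ankle, other", which makes nine site categories. A resident with a wrist or spine fracture and no recorded osteoporosis is high risk under the outcomes wording and not under the aims wording.

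**Step 2: can the intervention change membership?** Under the any-fracture wording, a vertebral fracture found through the stamp qualifies a resident directly, provided it reaches the record used. Under the hip-fracture wording it qualifies the resident only if osteoporosis is then documented. The checklist's attention to documenting diagnoses acts under both. Because it also covers assessment on admission, residents admitted after the start are exposed to it even if everyone present at the start is classified beforehand.

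**Step 3: does anything in the article remove this?** Blinding the person who downloads the data does not help if the underlying record differs by arm. The GEE model adjusts for age, gender, co-morbidities and number of medications. That does not undo selection into the analysed group.

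**Step 4: how large could the effect be?** All inputs here are assumed; none is in the article. Let D be the recorded high-risk residents in a home, t the share of them treated, a the residents added by extra recording, and q the share of those added who are treated. With no prescription changed:

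apparent difference = (D·t + a·q)/(D + a) − t = a(q − t)/(D + a)

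With D = 30 and a = 3 to 10 (+10% to +33%):

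| t | q = 0 | q = t | q = 1 |
|---|---|---|---|
| 30% | −2.7 to −7.5 | 0 | +6.4 to +17.5 |
| 50% | −4.5 to −12.5 | 0 | +4.5 to +12.5 |
| 70% | −6.4 to −17.5 | 0 | +2.7 to +7.5 |

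Entries are percentage points. For example, t = 70%, a = 10, q = 0 gives 10 × (0 − 0.70)/40 = −17.5. The sign is that of q − t, on which the article gives no information.

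**Step 5: a case where treatment does rise.** Assume that 25% of residents are recorded as high risk and 45% of those are treated, that recording rises by d = 5 or 10 points, that q = 10% or 30% of the added residents are newly treated, and that nobody else is treated. The outcome becomes (0.25 × 0.45 + d·q)/(0.25 + d):

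| d | q | Outcome (from 45%) | All residents treated (from 11.25%) |
|---|---|---|---|
| 5 points | 10% | 39.2% | 11.75% |
| 5 points | 30% | 42.5% | 12.75% |
| 10 points | 10% | 35.0% | 12.25% |
| 10 points | 30% | 40.7% | 14.25% |

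The fall follows from two of these assumptions: q lies below 45%, and treatment of known cases stays at 45%. A rise among known cases to (0.45 × 0.30 − 0.05 × 0.30)/0.25 = 48% cancels the mildest row, and a rise to (0.45 × 0.35 − 0.10 × 0.10)/0.25 = 59% cancels the worst. The table shows that a reversal is possible, not that it is expected.

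**The case against.** The strongest reply is that the article never says status is re-read at follow-up. The time points may date only the prescribing, the timeline figure is not shown, and a condensed article may leave the ascertainment rule to the full protocol or analysis plan. This stands. A reader might infer that the comparison is biased as planned; the text supports only a conditional risk.

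A reader might also infer that newly documented residents enter in the intervention arm alone. That goes too far. Control homes also record diagnoses and admit residents, and they received the provincial toolkit. The most that can be said is that recording may differ between arms. Nor does the article show that a fracture seen on X-ray reaches the record from which co-morbidities are drawn.

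It can also be said that an all-resident denominator answers a different question from the stated objective. That is correct, and it is why the all-resident analysis belongs beside the high-risk outcome rather than in its place.

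None of this touches the conflict between the two definitions. Leaving the ascertainment time to another document does not settle which definition that document would apply.

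**Conclusion.** The two definitions conflict and must be reconciled; this rests on the text alone. The denominator point holds conditionally: if high-risk status is read after the intervention starts, including for later admissions, membership can depend on allocation. The comparison is then open to bias of unknown size and direction. The range of −17.5 to +17.5 points rests entirely on assumed inputs and includes zero, which is reached when newly recorded residents are treated at the same rate as known cases. A claim that the sign of the effect will reverse is not supported.

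Severity is moderate. This is a secondary outcome of a pilot that emphasises feasibility. The primary vitamin D outcome is a proportion of residents without a risk restriction, so it is unaffected, as is the sample size.

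**What to change.** 1. Use one definition of high risk in both sections. Which one is the sponsor's choice. State whether fractures during the study count.
2. Keep the high-risk proportion as the stated secondary outcome, with high-risk status taken from the pre-intervention data pull for residents then present.
3. Add, as a sensitivity analysis, osteoporosis-medication prescribing among all residents at 6 and 12 months. Diagnosis recording cannot move this denominator, and it covers later admissions.
4. Label any proportion that uses high-risk status recorded at follow-up as descriptive.

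The cost is a wording change and one added analysis. No new data are needed, assuming that one of the prescribing pulls precedes the intervention; the timeline figure is not shown. The article says that no formal comparison of arms takes place before the end of the study, so the change can be made before results are seen. The downside is that the baseline-classified group omits residents admitted later, which matters where turnover is high, and the all-resident proportion will be lower and less clinically targeted.
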